## Abstract

**Introduction:**

Treating older adults with chemotherapy remains a challenge, given their under-representation in clinical trials and the lack of robust treatment guidelines for this population. Moreover, older patients, especially those with frailty, have an increased risk of developing chemotherapy-related toxicity, resulting in a decreased quality of life (QoL), increased hospitalisations and high healthcare costs. Phase II trials have suggested that upfront dose reduction of chemotherapy can reduce toxicity rates while maintaining efficacy, leading to fewer treatment discontinuations and an improved QoL. The DOSAGE aims to show that upfront dose-reduced chemotherapy in older patients with metastatic colorectal cancer is non-inferior to full-dose treatment in terms of progression-free survival (PFS), with adaption of the treatment plan (monotherapy or doublet chemotherapy) based on expected risk of treatment toxicity.

**Methods and analysis:**

The DOSAGE study is an investigator-initiated phase III, open-label, non-inferiority, randomised controlled trial in patients aged≥70 years with metastatic colorectal cancer eligible for palliative chemotherapy. Based on toxicity risk, assessed using the Geriatric 8 (G8) tool, patients will be stratified to either doublet chemotherapy (fluoropyrimidine with oxaliplatin) or fluoropyrimidine monotherapy. Patients classified as low risk will be randomised between a fluoropyrimidine plus oxaliplatin in either full-dose or with an upfront dose reduction of 25%. Patients classified as high risk will be randomised between fluoropyrimidine monotherapy in either full-dose or with an upfront dose reduction. In the dose-reduced arm, dose escalation after two cycles is allowed. The primary outcome is PFS. Secondary endpoints include grade≥3 toxicity, QoL, physical functioning, number of treatment cycles, dose reductions, hospital admissions, overall survival, cumulative received dosage and cost-effectiveness. Considering a median PFS of 8 months and non-inferiority margin of 8 weeks, we shall include 587 patients. The study will be enrolled in 36 Dutch Hospitals, with enrolment scheduled to start in July 2024. This study will provide new evidence regarding the effect of dose-reduced chemotherapy on survival and treatment outcomes, as well as the use of the G8 to choose between doublet chemotherapy or monotherapy. Results will contribute to a more individualised approach in older patients with metastatic colorectal cancer, potentially leading to improved QoL while maintaining survival benefits.

**Ethics and dissemination:**

This trial has received ethical approval by the ethical committee Leiden Den Haag Delft (P24.018) and will be approved by the Institutional Ethical Committee of the participating institutions. The results will be disseminated in peer-reviewed scientific journals.

**Trial registration number:**

NCT06275958.

STRENGTHS AND LIMITATIONS OF THIS STUDYThe uniqueness of this investigator-initiated trial lies in its design, specifically tailored for older patients.The choice between monochemotherapy and doublet chemotherapy will be individualised based on the Geriatric 8 Questionnaire.The DOSAGE trial measures meaningful endpoints relevant to older adults, such as quality of life, physical functioning and hospitalisations.As recruiting older adults in trials may be challenging, the study will be enrolled in 36 Dutch hospitals, with efforts to keep the participation burden low.To reduce the risk of undertreatment in the dose-reduced arm, the dose may be escalated after two cycles if there is good tolerability

## Introduction

 Colorectal cancer is one of the most frequently diagnosed cancers in older adults: 60% of patients with colorectal cancer are aged ≥65 years, with approximately one-third exceeding 75 years.^1^ Among them, half will eventually develop distant metastases or present with metastasised disease at time of diagnosis and will be needing chemotherapy. Yet, pivotal chemotherapy trials included very few older patients, and if included, they were generally very fit.^2^ This strongly limits the evidence base for the treatment of the majority of older adults with an average health status or frailty. Due to this lack of knowledge, there are no Dutch guidelines on how to tailor treatment for older adults with metastatic colorectal cancer, leading to high toxicity rates and unplanned hospitalisations and a reduced quality of life (QoL).^3^,^5^ This makes chemotherapy both less effective (due to early treatment discontinuation) and expensive for society. In addition, data from the Dutch cancer registry have showed no survival improvement for older patients with metastatic colorectal cancer in the past 10 years,^6^ suggesting that only a subset currently benefits from novel treatment options. Since society faces an ageing population as well as concerns of increasing healthcare costs, specific trials targeting this growing population are thus an unmet societal and medical need.

The main challenge in individualising treatment of older adults with metastatic colorectal cancer is the large heterogeneity between patients. While some patients are physically ‘fit’ and have few other concomitant diseases, others may have age-associated problems such as multimorbidity or physical or cognitive impairments, making them ‘frail’. These factors strongly influence the ability to endure chemotherapy.^4 5 7 8^ Older adults with metastatic colorectal cancer are commonly treated with either fluoropyrimidine-based monotherapy, or doublet chemotherapy with a fluoropyrimidine and oxaliplatin.^9^ High toxicity rates are seen in both regimens, but this effect is more pronounced in frail patients and in doublet chemotherapy.^10^ However, Dutch colorectal cancer guidelines do not give specific advice on the selection of older patients for either doublet chemotherapy or monotherapy in relation to risk of frailty or vitality,^11^ resulting in undesirable variations in treatment regimens across hospitals.

The Geriatric 8 (G8) Questionnaire is a geriatric screening tool that detects health deficits in different domains and risk of frailty in older patients.^12^ The tool has been well validated in oncology practice, with various studies demonstrating that older adults who score low on the G8 were more likely to experience chemotherapy-related toxicity compared with those with a normal G8 Score.^7 8 13^ The G8 serves as a simple and easy-to-use risk stratification tool for toxicity, offering a practical alternative to the geriatric assessment (GA), which is much more time-consuming and ideally should be done by trained staff. Additionally, the G8 tool is already widely used in Dutch hospitals, as underscored by a recent study showing that 97% of Dutch hospitals offering colorectal cancer surgery use the G8 for frailty screening,^14^ which will facilitate its implementation. Therefore, the G8 can be used for a tailor-made treatment decision between monotherapy or doublet chemotherapy.

Another potential solution to reduce toxicity risk is to perform upfront dose reduction of chemotherapy. Prior studies demonstrated that upfront dose reduction of chemotherapy in older adults with advanced cancer decreased toxicity rates by 20%–30%, while maintaining efficacy.^15 16^ For example, the phase II NORDIC9 trial compared full-dose S1 monotherapy with upfront dose-reduced S1 with oxaliplatin in 160 older adults with metastatic colorectal cancer judged ‘unfit’ for full-dose treatment by their oncologist.^16^ The study showed that doublet chemotherapy with upfront dose reduction resulted in a better progression-free survival (PFS) (6 months for reduced dosed vs 5 months for full dose), with markedly reduced toxicity rates in the dose-reduced arm (43% vs 62%, respectively). In addition, the GO2 trial compared different levels of dose-reduced capecitabine plus oxaliplatin (CAPOX) in 559 advanced gastro-oesophageal cancer patients deemed unfit for full-dose chemotherapy. Results showed that upfront dose-reduced chemotherapy was non-inferior to full-dose treatment and resulted in an improved toxicity profile, even in less frail patients.^17^ Thus, dose-reduced chemotherapy can improve QoL and physical functioning and decrease hospital admissions. Despite these promising results, upfront dose reduction is not yet widely adopted in Dutch daily practice and has not yet been studied in a phase III study or in chemotherapy schemes used in the Dutch setting.

### Study objectives

The primary objective of the DOSAGE study is to show that upfront dose-reduced chemotherapy in patients with metastatic colorectal cancer is non-inferior to full-dose treatment in terms of PFS with adaption of the treatment plan (monotherapy or doublet chemotherapy) based on expected risk of treatment toxicity for the individual patient. Secondary objectives are to investigate that upfront dose-reduced chemotherapy will lead to lower toxicity rates, better QoL and physical functioning, less dose reductions, treatment withdrawals and hospital admissions, a better overall survival (OS), a higher cumulative received dose and lower healthcare costs.

## Methods

### Study design

The DOSAGE study is an investigator-initiated, phase III, open-label, non-inferiority, randomised controlled clinical trial. The trial will enrol patients in 36 Dutch hospitals (2 academic and 34 peripheral hospitals). A list of all participating hospitals can be found at clinicaltrials.gov (NCT06275958).

### Patient population

Patients aged 70 years or older with colorectal cancer and metastasis without localised treatment options, eligible for first-line palliative chemotherapy at the discretion of the treating oncologist, will be included. Patients who received prior adjuvant chemotherapy in the year before inclusion, candidates for triplet therapy and those with a complete or incomplete dihydropyridine dehydrogenase deficiency or microsatellite instability-high colorectal cancer or with grade≥2 peripheral polyneuropathy are ineligible.

### Intervention

Participants will be enrolled by their treating physician. All participants will first undergo geriatric screening by the G8 tool. Based on the G8, participants with a ‘low risk of toxicity’ (G8 Score of 15 or higher) will be stratified to doublet chemotherapy and those with a ‘high risk of toxicity’ (G8 Score of 14 or lower or judged as ‘high toxicity risk’ at the discretion of the treating oncologist) will be stratified to monotherapy (figure 1). Participants will then be randomised in a 1:1 ratio using block randomisation via the Castor electronic data capture (EDC) by the Clinical Research Center. Patients will be randomised between upfront dose-reduced chemotherapy or full-dose chemotherapy. In the dose-reduced intervention arm, dose escalation after two cycles is allowed, as explained in detail below. In the randomisation process, patients will be stratified by additional targeted therapy, tumour side and hospital.

**Figure 1 F1:**
[figure not shown]
Schematic overview of study design. CRC, colorectal cancer; G8, Geriatric 8; PFS, progression-free survival.

### Fluoropyrimidine monotherapy

Patients classified as ‘high risk of toxicity’ will be randomised between monotherapy with a fluoropyrimidine in either full-dose or with an upfront reduction. The following dosing scheme is allowed in the full-dose arm:

Capecitabine 1000 mg/m^2^ at day 1–14 (every 3 weeks) (see Discussion for rationale).

In the dose-reduced arm, patients receive an upfront 25% reduction (75% of full dose, 750 mg/m^2^).

### Doublet chemotherapy

Patients classified as low risk will be randomised between doublet chemotherapy with a fluoropyrimidine (physicians’ choice fluorouracil (5-FU) or capecitabine) and oxaliplatin in either full-dose, or with an upfront dose reduction. In the full-dose arm, the following dosing schemes are allowed:

CAPOX: capecitabine 1000 mg/m^2^ at day 1–14 (every 3 weeks) and oxaliplatin 130 mg/m^2^ at day 1 (every 3 weeks).FOLFOX6: 5-FU 400 mg/m^2^ intravenous bolus at day 1 followed by 2400 mg/m^2^ in 46 hours (every 2 weeks), leucovorin 400 mg/m^2^ day 1 (every 2 weeks) and oxaliplatin 85 mg/m^2^ day 1 (every 2 weeks).

In the dose-reduced arm, patients receive an upfront 25% reduction (75% of full dose).

Addition of targeted treatment (bevacizumab or epidermal growth factor receptor (GFR) inhibition) is allowed. Patients with a moderate renal impairment (GFR 30–50 mL/min) will receive a 25% reduced starting dose of capecitabine in the full-dose arm and a 40% reduced starting dose in the dose-reduced arm.

### Treatment monitoring

After each treatment cycle, treatment tolerability (chemotherapy-related toxicity according to the Common Terminology Criteria for Adverse Events (CTCAE) V.5.0^18^) will be assessed. Patients in the upfront dose-reduced arm who have tolerated the first two cycles of their treatment well (no occurrence of grade 2–5 toxicity), can (but do not have to) receive dose-escalation to 100% at the discretion of the treating oncologist and after consultation with the patient. In both arms, toxicity may allow for further dose reductions: if patients experience either grade 3–4 toxicity or unacceptable grade 1–2 toxicity that influences QoL, the oncologist can reduce the dose by 25%. The minimal dose is 50% of full dose: if further (unacceptable) toxicity occurs, the treatment should be discontinued. For neuropathy, in case of grade 2 toxicity, oxaliplatin dose is reduced with 25%. In case of grade 3 neuropathy, oxaliplatin is definitively stopped. After 18 weeks of doublet chemotherapy, maintenance therapy with capecitabine or 5-FU (with or without bevacizumab) can be started at the discretion of the treating oncologist. Chemotherapy treatment will be continued until progression, unacceptable toxicity or a patients’ or clinicians’ decision to stop. If patients develop progression or discontinue first-line treatment due to other reasons (such as toxicity), the study will end and any further treatment lines are allowed by the discretion of the oncologist.

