### Study procedures

Apart from the G8 that is performed to stratify patients between monotherapy and doublet therapy, participants will also undergo a GA. The results from the GA will be used to characterise the study population and find predictors of poor outcomes. The GA will comprise the EuroQol-5D (EQ-5D)^19^ and European Organisation for Research and Treatment of Cancer (EORTC) Core QLQ-C30 questionnaires for QoL, the Katz Activities of Daily Living (ADL),^20^ Lawton Instrumental ADL (IADL)^21^ and home and informal care for physical functioning, the Modified Telephone Interview for Cognitive Status for cognition,^22^ Mini Nutritional Assessment for malnutrition^23^ and Patient Health Questionnaire-2 for mood^24^ (table 1). The GA will be conducted via telephone calls to increase feasibility. Performing a telephone-based GA has proven to be feasible in previous studies with older adults.^25 26^ Comorbidity (assessed with the Charlson Comorbidity Index^27^) and polypharmacy (at least five different types of medication) will be obtained from the medical charts. If the GA identifies geriatric deficits, the treating oncologist will be informed and GA-based interventions will be at their discretion.

**Table 1 T1:** Overview of study procedures

	Screening (T<0)	Prerandomisation	Randomisation (T=0)	Before and after every cycle, until progression	Each 8–12 weeks	After 1 month	After 3 months	After 6 months	After 9 months	After 12 months	End of study
Informed consent		E									
Geriatric-8		E									
Inclusion/exclusion	X										
Patient/tumour characteristics	X										
Laboratory analysis*	X			X							
Toxicity				X							
Radiologic evaluation†	X				X						
Dose reductions				X							
Cycles, n				X							
Hospitalisations				X							
Survival					X						X
EQ-5D‡		E				E	E	E	E	E	
EORTC Core QLQ-C30‡		E				E	E	E	E	E	
Katz ADL‡		E				E	E	E	E	E	
Lawton IADL‡		E				E	E	E	E	E	
Home and informal care‡		E				E	E	E	E	E	
MNA		E									
TICS-M		E									
PHQ-2		E									

Window for questionnaires: ±4 weeks.

X=procedures are standard of care. E=extra procedure in study context.

* Laboratory analyses should at least include total blood count, kidney and liver function.

† Radiologic evaluation: performed according to local standard practice (CT scan, positron emission tomography (PET) scan and/or MRI scan).

‡ Follow-up questionnaires will be performed until disease progression or until 12 months after randomisation in case of no disease progression.

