### Outcome measures

The *primary outcome* of the study is PFS, defined as time from randomisation until either radiological or clinical progression or death due to any cause, whichever occurs first. Timepoints of measurements are presented in table 1. In case of clinical progression as judged by the local principal investigator, local investigators should explain the base of clinical progression. *Secondary endpoints* include QoL (measured by the EQ-5D and EORTC Core QLQ-C30 questionnaires after 1, 3, 6, 9 and 12 months), physical functioning (measured with the Katz ADL, the Lawton IADL and home and informal care after 1, 3, 6, 9 and 12 months), grade≥3 chemotherapy-related toxicity according to the CTCAE during study treatment, dose reductions during study treatment, number of treatment cycles, unplanned hospital admissions within the first year, OS, cumulative received dose and cost-effectiveness in the first year. Predictive geriatric markers of poor outcomes will be identified using the baseline GA.

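### The sentence that ends the study when first-line treatment stops conflicts with PFS and OS follow-up and, if applied literally, would lose primary-endpoint events

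*Protocol article*

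**What the plan says.** Treatment monitoring in the protocol article first sets out how long chemotherapy continues. It then says: "If patients develop progression or discontinue first-line treatment due to other reasons (such as toxicity), the study will end", and adds that "any further treatment lines are allowed by the discretion of the oncologist". This is the article's only statement of what happens to a patient when first-line treatment stops.

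Other sections describe follow-up that does not depend on treatment:

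- Outcome measures defines PFS as "time from randomisation until either radiological or clinical progression or death due to any cause, whichever occurs first". Stopping treatment is neither an event nor a stated censoring point.
- The same section lists among the secondary endpoints "unplanned hospital admissions within the first year, OS, cumulative received dose and cost-effectiveness in the first year".
- Table 1 (Study procedures) schedules imaging and survival every 8 to 12 weeks, and survival again at end of study. Both are marked as standard of care. One footnote says "Radiologic evaluation: performed according to local standard practice"; another says "Follow-up questionnaires will be performed until disease progression or until 12 months after randomisation in case of no disease progression".
- Statistics: analysis plans an intention-to-treat analysis alongside a per-protocol one, with patients grouped as randomised.
- Study objectives expects the reduced-dose arm to have "less dose reductions, treatment withdrawals and hospital admissions".

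**The concern.** PFS needs observation until progression or death, and OS needs it until death. The Treatment monitoring sentence, read as written, ends observation of some patients before the primary endpoint has occurred and of all patients before OS is complete. A patient who stops for toxicity without progression would have no PFS data after that date, so the analysis could only use the time up to the stop.

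Such stops are not neutral dropout. They are related to treatment, they are decided in an open-label trial, and the protocol expects fewer of them in one arm. The Introduction also argues that early discontinuation makes chemotherapy less effective, so the trial's own rationale links stopping to outcome. The Discussion argues that later treatment does not bias PFS, but it does so for patients who have already progressed. That argument does not cover a patient who stops for toxicity and starts another line before progression.

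At stake are the number of PFS events, hence power, and possibly the hazard ratio that is compared with 1.25. With 36 hospitals, sites may also read the sentence differently.

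**Working it through.** **1. The passages side by side**

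| Section | Follow-up runs to |
|---|---|
| Treatment monitoring | progression or any other stop of first-line treatment |
| Outcome measures, PFS | progression or death |
| Outcome measures, OS | death |
| Table 1, imaging and survival | every 8 to 12 weeks; no end at treatment stop stated |
| Table 1, questionnaires | progression or 12 months |
| Statistics: analysis | all patients as randomised (intention-to-treat) |

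Read literally, the first row agrees with none of the others. It also ends the study at progression, which would leave OS unobserved after every progression.

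**2. The plan's own sample size**

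Inputs from Statistics: sample size and power calculations: margin HR 1.25, true HR 1, hazard 0.12 per period, 5% significance, 80% power, accrual over 36 of 48 periods, 264 patients per arm. I take the 5% as one-sided, because a two-sided 5% gives 668 patients and does not reproduce the plan.

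- Events (Schoenfeld): 4 × (1.645 + 0.842)² / (ln 1.25)² = 497 after rounding up.
- Probability of an event: 1 − (e^(−0.12×12) − e^(−0.12×48)) / (0.12 × 36) = 1 − (0.2369 − 0.0032)/4.32 = 0.946.
- Patients: 497/0.946 = 526 after rounding up (530 with Freedman's formula), against 528 stated.
- With 528 patients: 528 × 0.9459 = 499 events, and power Φ(√499 × 0.2231/2 − 1.645) = 80.2%.
- Dropout: 528/0.90 = 587, as stated.

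The plan's figures reproduce when PFS is followed past treatment stop.

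**3. Events and power if PFS ends at treatment stop**

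The documents give no stopping rate, so the shares f who stop before progression are assumptions. With stopping unrelated to prognosis, the stopping hazard is c = 0.12 × f/(1 − f). With k = 0.12 + c, the probability of an observed PFS event is (0.12/k) × [1 − (e^(−12k) − e^(−48k))/(36k)].

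Example for 20% versus 10%:

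- Full dose: c = 0.030, k = 0.150, probability 0.776.
- Reduced dose: c = 0.0133, k = 0.1333, probability 0.862.
- Events: 264 × (0.776 + 0.862) = 432. Power: Φ(√432 × 0.2231/2 − 1.645) = 75.0%.

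| Assumed stopping, full/reduced | Events | Power |
|---|---|---|
| none censored | 499 | 80.2% |
| 10%/5% | 467 | 77.8% |
| 20%/10% | 432 | 75.0% |
| 30%/15% | 397 | 71.9% |

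**4. The hazard ratio**

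A simulation with one million patients per setting linked time to stopping and time to PFS event through a Gaussian copula with correlation ρ, with administrative follow-up of 12 to 48 periods. A positive ρ means that patients who stop early also tend to progress early. Stopping shares and ρ are assumptions. The table shows the HR estimated when PFS is censored at the stop.

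| ρ | True HR 1.00: 20%/10% | True HR 1.00: 30%/15% | True HR 1.25: 20%/10% | True HR 1.25: 30%/15% |
|---|---|---|---|---|
| −0.5 | 0.940 | 0.914 | 1.197 | 1.169 |
| 0 | 0.999 | 1.005 | 1.250 | 1.252 |
| 0.3 | 1.029 | 1.040 | 1.287 | 1.303 |
| 0.5 | 1.046 | 1.072 | 1.312 | 1.338 |
| 0.7 | 1.067 | 1.105 | 1.342 | 1.388 |

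Full follow-up recovered the true HR in every setting, to within simulation error. Different stopping rates alone give no bias (ρ = 0). With ρ above 0 the error works against non-inferiority; with ρ below 0 it works towards it.

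**The case against.** The strongest reply is that the sentence was never meant as a follow-up rule. It stands under Treatment monitoring, follows a statement on how long chemotherapy continues, and goes on to permit further treatment lines. Because it also ends the study at progression, the literal reading would defeat the OS endpoint. The PFS definition, Table 1 and the intention-to-treat analysis all point to continued follow-up, and detailed censoring rules belong in an analysis plan that is not shown.

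Much of this stands. It makes it likely that the end of study treatment was meant, and the absence of a censoring rule from an article is not the fault here. It does not remove the conflict, because the sentence is a stated rule. Table 1 does not settle the matter either: imaging follows local practice without a statement that it continues after a stop, and survival is collected up to an end of study that Treatment monitoring appears to place at the stop. The 10% dropout allowance is not said to cover these patients.

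A reader might infer more: that the protocol censors PFS and OS at treatment stop, and that this inflates false non-inferiority because clinicians would stop an apparently ineffective reduced dose just before progression. The documents do not support this. No section says that either endpoint is censored there. Outcome measures counts clinical progression, judged and explained by the local investigator, as a PFS event, so a stop for apparent failure would plausibly be recorded as an event.

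**Conclusion.** The point holds as an internal conflict with conditional consequences. The Treatment monitoring sentence cannot be followed literally while PFS, OS, the Table 1 schedule and the intention-to-treat analysis are carried out as described.

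If it is followed literally, PFS events are lost. For assumed stopping of 10%/5% to 30%/15%, unrelated to prognosis, events fall from 499 to between 467 and 397, and power from 80% to between 78% and 72%. These figures rest on exponential PFS with the plan's hazard of 0.12, 528 patients and a one-sided 5% level.

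Bias in the hazard ratio is a further possibility, only if stopping is related to prognosis. Neither its size nor its direction follows from the documents. If follow-up does continue after treatment stop, neither consequence arises and only the wording is at fault.

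**What to change.** Reconcile Treatment monitoring with Outcome measures, Table 1 and Statistics: analysis by stating that:

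- progression or discontinuation of first-line treatment ends study treatment only;
- patients who stop without progression remain in the existing 8-to-12-weekly standard-of-care imaging follow-up until progression or death;
- all patients are followed for survival;
- stopping treatment or starting another line is not a censoring event in the intention-to-treat PFS analysis. Censoring at the stop may be kept as a sensitivity analysis.

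All participating hospitals should receive the same clarification, because progression dates that were not recorded at the time are hard to recover later. The change does not touch the rules on when treatment is stopped.

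The cost is small: one sentence replaced, and continued chart extraction after treatment stop. Table 1 already marks imaging and survival as standard of care.
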